### Patient Randomization

The study population will be allocated to each of the intervention groups using randomization in blocks. Block size will be kept secret to all study related personnel. Participants will be numbered sequentially. It is expected that after the randomization there will be no differences in the clinical or biochemical characteristics among different treatment groups at the start of post-operative parenteral fluid therapy. After randomization, the anesthetist and the clinical team will be informed by the surgeon to which fluid regimen arm the patient has been allocated.

### Clinical and Laboratory Assessment

Upon admission from surgery and by the end of the first post-operative day, patients will be weighted (kg). In addition, height (m) will be measured and body mass index (kg/m^2^) calculated. Non-invasive blood pressure (mm Hg), heart rate (beats per minute), monitoring of arterial oxygen saturation with pulse oximetry, and body temperature will be recorded at regular intervals.

Blood samples will be collected immediately after the conclusion of surgery (T_0_), at 6 h (T_6_) and 12 h (T_12_), and then at 24 h (T_24_) following the surgery. The blood samples obtained at T_0 _and T_24 _will be analyzed for plasma (p) Na^+^, K^+^, Cl^-^, creatinine, urea, uric acid, glucose, lactate, ketones, renin, aldosterone, ADH, hemoglobin, blood gas, and for serum (s) osmolality by means of routine and quality controlled laboratory techniques. Serum Cortisol and s-TSH (thyroid-stimulating hormone) will be measured at T_0_. At T_12_, p-Na^+^, p-glucose, and blood gas will be monitored. The blood samples obtained at T_6 _and T_12 _will be analyzed for p-Na^**+**^. Also, at the discretion of the treating anesthesiologist, p-Na^+ ^will be monitored at intermediate sampling if p-Na^+ ^at T_12 _follows a decreasing trend.

Entire urine collection from T_0 _to T_24 _will be obtained by urine bag or clean catch, as appropriate. A bladder scan will be performed whenever urinary retention is suspected. Depending on the bladder volume measured, urethra catheterization will be performed to relieve urine retention if the patient cannot void on his/her own. Adequacy of timed urine collection will be confirmed as far as possible by estimation of urinary creatinine excretion rate (mmol/kg per 24 h) [35].

In addition to measuring total urine volume, urinary sodium, potassium, and chloride excretion, we will calculate, from spot urine samples obtained at T_0 _and T_24_, the fractional excretion of sodium (FeNa), the fractional excretion of uric acid (FeUA), and the urine osmolality.

The FeNa [(u-Na^+ ^× p-creatinine) ÷ (p-Na^+ ^× u-creatinine) × 100] is the fraction of sodium filtered by the glomeruli that appears in the urine. The extracellular fluid compartment is regulated by changes in sodium excretion and when the extracellular fluid is contracted (e.g., intra-operative hypovolemia due to blood loss), urinary sodium can be undetectable. The FeNa is therefore a useful laboratory investigation to differentiate hypovolemic, i.e., a decrease of the effective arterial blood volume, from euvolemic state [36]. On the other hand, hypervolemic state enhances FeNa, an effect independent of the increase in urinary flow.

In the event of non-osmotic excess secretion of ADH, as it has been observed in post-operative patients, generous intake of solute-poor fluid might result in a positive water balance. If post-operative fluid prescription is however limited, as we intend in our study, the extracellular fluid compartment (and total body fluid) will not be expected to expand. Consequently, the FeNa at T_24 _should not be significantly different compared to T_0_.

Uric acid urinary excretion is regulated to changes in the effective arterial blood volume [37]. Therefore, FeUA [(u-UA × p-creatinine) ÷ (p-UA × u-creatinine) × 100] is also useful to indirectly infer the effective arterial blood volume, provided that the renal proximal tubule is properly functioning. This and the aforementioned laboratory investigations will provide an insight into how a child's kidneys are handling water and salt.

Urine analysis, including osmolality, will be performed by using routine and quality controlled techniques. Taken together, FeNa, FeUA, total urinary electrolyte excretion, urine osmolality, ADH, as well as p-renin and p-aldosterone activity will be interpreted in the context of the patient's water and electrolyte balance.

Finally, serum (~3 ml), and urine samples (~15 ml), obtained at T_0 _and T_24 _will be stored -80°C in a biobank (duration of storage 10 years) for eventual future analysis.

### Parenteral Fluid Therapy

*Intra-operative fluid management*: following our routine procedure, the volume of intra-operative fluid will be adapted to the severity of surgical trauma as follows; *i) *mild trauma, 5 ml/kg body weight (BW) per h, *ii) *moderate trauma, 7.5 ml/kg BW per h, and *iii) *severe trauma, 10 ml/kg BW per h. The parenteral fluid used intra-operatively, i.e., from the start of the surgery to T_0_, will consist of 0.40% salt solution (70 mmol/L Na^+ ^+ 45 mmol/L Cl^- ^+ 25 mmol/L acetate) in 2.5% glucose (B. Braun Melsungen AG, Melsungen, Germany).

During surgery, appropriate amount of intravenous isotonic fluid blouses will be administered whenever hypovolemia is suspected to ensure adequate intravascular volume and oxygen delivery. The duration of anesthesia and all intra-operative inputs will be documented in the medical record. In addition, we will have free and open access to data concerning patient's pre-operative intravenous fluid therapy.

*Post-operative fluid management*: the fluid needs for parenteral therapy will be estimated based on metabolic requirements of the body, i.e., expenditure of energy, as described by Holliday and Segar where daily caloric expenditure is equal to 100 cal/kg BW up to 10 kg, 1000 cal + 50 cal/kg BW from 11 to 20 kg, and 1500 cal + 20 cal/kg BW over 20 kg [22]. Under normal conditions, the average needs of water for replacement of usual insensible and urinary water losses is directly related to the metabolic rate, and when expressed in milliliters, equals the estimated daily energy expenditure in calories [22]. Depending on age, the amount of water that accounts for insensible water losses varies from 45 to 59 ml/100 cal per 24 h, while the replacement of urinary water losses will depend on the renal solute load, i.e., the total daily excretion of solutes, and the concentration of these solutes in the urine [22]. Holliday and Segar estimated that a solute load of 40 mosmol/100 cal per 24 h, a figure expected in the instance of rational parenteral fluid therapy, would require ~60 ml of water to be excreted, i.e., 60 ml/100 cal per 24 h. This figure was calculated at a urine osmolality of 600 mosmol/kg H_2_0, which was considered the maximum to safely be expected from patients receiving parenteral fluid therapy under normal conditions [22].

Since prescription of intravenous fluid therapy given at full maintenance rate may be potentially dangerous when renal water excretion is limited by ADH excess, parenteral fluid therapy will be given at a lower rate than the recommended average maintenance rate [8]. Consequently, and, in accordance with our local care guidelines for parenteral fluid therapy following surgical procedures, ~¾ of the average maintenance rate will be prescribed for the first 24 h post-operatively, i.e., from T_0 _to T_24_. Table 1 relates body weight to ~¾ of the average maintenance allowances for hourly periods.

**Table 1 T1:** 24 h post-operative fluid volume at ~¾ of average maintenance rate according to Holliday-Segar formula.

Weight (kg)	ml/kg/24 h
10	80
11	76
12	73
13	71
14	69
15	67
16	65
17	64
18	62
19	61
20	60
22	56
24	53
26	51
28	49
30	47
35	43
40	40
45	38
50	36
55	35
60	33
65	32
70	31

Ongoing post-operative losses, e.g., nasogastric drainage following abdominal surgery, will be replaced ml for ml with Ringer's lactate solution.

Below, we describe an example of the likely change in p-Na^+ ^that would result at T_24 _in a previously healthy 10 year-old-boy who met the inclusion criteria to participate in the study. We presuppose that our hypothetical case has been randomized to be treated with 0.23% salt solution in 5% glucose. We assume that, similar to patients we expect will participate in our study, his kidneys are capable of generating concentrated urine in response to non-osmotic stimulated ADH activity. Since in the immediate post-operative period a child with intact urinary concentration ability may achieve urine osmolality of more than 700 mosmol/kg H_2_O as a result of elevated ADH levels [38], in our example we arbitrarily set the urine osmolality at 900 mosmol/kg H_2_O.

In this hypothetical case we take into account all the patient's inputs during the 24 h period following surgery, i.e., total volume of water, Na^+^, K^+^, and Cl^-^. Each element is analyzed separately and it is supposed that all the infused Na^+^, K^+^, and Cl^- ^represent the renal solute load that eventually will be excreted in the urine [39]. Thus, one mmol of each of these elements equals one mosmol. Since glucose is metabolized to carbon dioxide and water, it does not contribute to renal solute load in our example. Similarly, in solutions containing acetate, this anion is metabolized in the liver and does not contribute to renal solute load.

It should be noted that, for the sake of simplicity, we have chosen to take for granted that in this hypothetical case the urine osmolality would be fixed during the 24 h period following surgery. This, and the fact we only consider the patient's input of water and electrolyte, might confine the accuracy in our predicting p-Na^+ ^at T_24_. Therefore, in our study, the patient's expected p-Na^+ ^at T_24 _will be calculated by computing actual water and electrolyte balance during the first 24 h post-operatively as follows:

where the subscripts _f _and _i _represents final (T_24_) and initial (T_0_) p-Na^+^, respectively; Δ (Na^+ ^+ K^+^) represents cation input (infused) minus cation output (urinary excretion); TBW represents the estimated initial total body water and ΔTBW describes the water infused minus water excreted, respectively.

In our study we will analyze, by applying the same approach as described in our hypothetical case, whether p-Na^+ ^at T_24 _can be correctly estimated by using the patient's immediate postoperative urine osmolality value. The estimated p-Na^+ ^obtained by this method and by means of water and electrolyte balance will be plotted against the patient's actual p-Na^+ ^measured at T_24 _for assessing agreement between methods [40].

Twenty-four hour insensible water losses in each participant will be calculated as follows:

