**Methods/Design:**

Our prospective randomized non-blinded study will be conducted in healthy children and adolescents aged 1 to 14 years who have been operated for acute appendicitis. Patients will be randomized either to intravenous hypotonic (0.23% or 0.40% sodium chloride in glucose, respectively) or near-isotonic (0.81% sodium chloride in glucose) solution given at approximately three-fourths of the average maintenance rate. The main outcome of interest from this study is to evaluate 24 h post-operatively whether differences in p-Na^+ ^between treatment groups are large enough to be of clinical relevance. In addition, water and electrolyte balance as well as regulatory hormones will be measured.

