### Example

Weight = 30 kg. P-Na^+ ^at T_0 _= 140 mmol/L.

24 h infused volume according to study protocol (Table 1) = 1410 ml.

24 h insensible (~45 ml/100 cal per 24 h) = 765 ml [22].

The expected 24 h urine output needed to maintain water balance will be as follows: infused volume - insensible losses = 645 ml.

By infusing 0.23% salt solution (40 mmol/L Na^+ ^+ 20 mmol/L K^+ ^+ 60 mmol/L Cl^-^) in 5% glucose, the electrolyte intake (and therefore excretion) will be expected to be as follows:

At a fixed urine osmolality of 900 mosmol/kg H_2_O, because of hypothetically persistent ADH release, our example case will be expected to produce 188 ml urine per 24 h (i.e., solute load of 169.2 mosmol ÷ urine osmolality of 900 mosmol/kg H_2_O) [22]. As a consequence, 457 ml of water will be retained (645 ml - 188 ml); ⅔ of this will distribute to the intracellular fluid compartment and ⅓ to the extracellular fluid compartment [41]. Since the apparent volume of distribution of sodium is the total body water (TBW) [42], and the estimated TBW accounts for 60% of body weight [43], the expected change in p-Na^+ ^can be treated algebraically as follows:

where the subscripts _i _and _f _represent initial and final states, respectively. This equation states that the initial volume × initial concentration = final volume × final concentration. Since we assume that in our hypothetical case there will be no change in total body sodium content by the end of the first postoperative 24 h, the p-Na^+^_f _is now the original sodium content divided by TWB_f_. Thus, in our example the p-Na^+^_f _will be expected to be 136.5 mmol/L (i.e., p-Na^+^_f _= 18 L × 140 mmol/L ÷ 18.457 L).

If we replace 0.23% sodium chloride parenteral fluid therapy with either 0.40% sodium chloride or 0.81% sodium chloride, the expected p-Na^+^_f _would be 136.4 mmol/L and 138.2 mmol/L, respectively.

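### Table 1 is labelled about three-fourths of Holliday-Segar maintenance, but its volumes are about 80% of that formula in lighter children and rise to 86–87.5% from 50 kg

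*Protocol article*

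**What the plan says.** The abstract describes each fluid as a "solution given at approximately three-fourths of the average maintenance rate". The Background gives the same fraction, ~¾, for the hospital's routine regimen. The Parenteral Fluid Therapy section repeats it for the trial: ~¾ "of the average maintenance rate will be prescribed for the first 24 h post-operatively".

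That section also defines full maintenance. Daily energy expenditure is set at 100 cal for each kg in children of 10 kg or less; for heavier children it is "1000 cal + 50 cal/kg BW from 11 to 20 kg, and 1500 cal + 20 cal/kg BW over 20 kg". The water requirement, "when expressed in milliliters, equals the estimated daily energy expenditure in calories", so 1 cal corresponds to 1 ml.

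Table 1 lists 24 body weights from 10 to 70 kg with volumes in ml/kg/24 h. Its caption says that these are ~¾ of average maintenance by the Holliday-Segar formula. The sentence introducing it says that the table relates body weight to ~¾ "of the average maintenance allowances for hourly periods".

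The Example section applies the table to a 30 kg child: "24 h infused volume according to study protocol (Table 1) = 1410 ml". It puts that child's insensible losses at 765 ml, at about 45 ml per 100 cal.

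**The concern.** The fraction, the formula and the table are three statements of one regimen, and they do not agree. The reduced rate is a defining feature of this trial: the protocol justifies it by the danger of full-rate fluid when ADH limits water excretion, and it expects no expansion of the extracellular compartment because the volume is limited. The Discussion treats infusion rate as an open question in its own right when it reviews earlier studies. If the trial is reported as a three-fourths regimen, a reader who computes that fraction from the formula will arrive at a smaller volume than the one studied, and the gap will depend on the child's weight.

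**Working it through.** **Inputs.** Formula and 1 ml per cal: Parenteral Fluid Therapy. Volumes: Table 1. Check on how the formula is read: Example.

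**Reading the formula.** With w the weight in kg, full maintenance M(w) in ml/24 h is 100w up to 10 kg, 1000 + 50(w − 10) from 11 to 20 kg, and 1500 + 20(w − 20) above 20 kg. The Example confirms this: 765 ml ÷ 0.45 ml per cal = 1700 cal, and M(30) = 1500 + 20 × 10 = 1700 ml. Applying the 20 cal/kg to total weight would give 1500 + 20 × 30 = 2100, which contradicts the Example.

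**Table against formula.** Ratio = (Table 1 ml/kg × w) ÷ M(w). Selected rows:

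| Weight (kg) | Table 1 (ml/kg) | Table volume (ml) | M(w) (ml) | Ratio | ¾ × M(w) (ml) | Excess over ¾ (ml) |
|---|---|---|---|---|---|---|
| 10 | 80 | 800 | 1000 | 80.0% | 750 | 50 |
| 20 | 60 | 1200 | 1500 | 80.0% | 1125 | 75 |
| 30 | 47 | 1410 | 1700 | 82.9% | 1275 | 135 |
| 40 | 40 | 1600 | 1900 | 84.2% | 1425 | 175 |
| 50 | 36 | 1800 | 2100 | 85.7% | 1575 | 225 |
| 55 | 35 | 1925 | 2200 | 87.5% | 1650 | 275 |
| 70 | 31 | 2170 | 2500 | 86.8% | 1875 | 295 |

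Over all 24 rows the ratio runs from 79.6% (11 kg) to 87.5% (55 kg). From 10 to 24 kg it stays between 79.6% and 80.6%, and from 26 kg it climbs. The ¾ columns only measure the discrepancy; they are not a proposed rate.

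**Rounding.** Subtracting 0.5 ml/kg from every row still leaves a minimum of 79.1%, so rounding to whole ml/kg does not explain the gap.

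**Where the drift comes from.** Every row equals, after rounding, 80 ml/kg for the first 10 kg, 40 ml/kg for the next 10 kg and 20 ml/kg above 20 kg. At 40 kg, for example, (800 + 400 + 400) ÷ 40 = 40. The protocol does not state this rule; it is inferred from the fit. On it, the first two bands are cut to 80% of the formula (80/100 and 40/50) and the third is not cut (20/20), which is why the ratio rises with weight.

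**The worked example.** The protocol's method at 1410 ml takes infused volume minus insensible losses, 1410 − 765 = 645 ml; urine = solute load ÷ 900 mosmol/kg; and final p-Na = 18 × 140 ÷ (18 + retained litres).
- 0.23%: load 120 × 1.41 = 169.2 mosmol, urine 188 ml, retained 457 ml, p-Na 136.5 (printed 136.5).
- 0.40%: load 115 × 1.41 = 162.15 mosmol, urine 180 ml, retained 465 ml, p-Na 136.48 (printed 136.4).
- 0.81%: load 264 × 1.41 = 372.24 mosmol, urine 414 ml, retained 231 ml, p-Na 138.2 (printed 138.2).

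At 1275 ml, water above insensible losses is 1275 − 765 = 510 ml.
- 0.23%: urine 170 ml, retained 340 ml, p-Na 137.40.
- 0.40%: urine 163 ml, retained 347 ml, p-Na 137.35.
- 0.81%: urine 374 ml, retained 136 ml, p-Na 138.95.

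The largest predicted fall is therefore 140 − 137.35 = 2.65, about 2.6 mmol/L. At the table volume it is 140 − 136.48 = 3.52, about 3.5 recomputed, against 3.6 as printed. The like-for-like change is about 0.9 mmol/L.

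**The case against.** The protocol never claims exactly three-fourths: it uses an approximation sign or the word approximately each time. That stands for the lighter children, where about 80% can loosely pass as an approximation, so it would be too strong to call every row an error. It does not stand further up the table. An approximation would scatter around 75%; these ratios all lie above it and grow with weight. At 55 kg the cut from full maintenance is 12.5%, half of the 25% that the label implies.

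It can also be said that the volumes are open. Table 1 prints them row by row, and the Example treats them as the protocol volume, so a site can reproduce what is to be given. This stands too. A reader might infer that patients would receive an undisclosed volume, but what is wrong is the description: the fraction and its attribution to the formula.

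Three further inferences are tempting and are not supported.
- **A biased comparison.** All three arms take their volume from the same table, so the between-arm contrast in p-Na at 24 h is not biased by the label.
- **A wrong sample size.** The Sample size calculation section sets the 5 mmol/L margin arbitrarily, says that the illustrative fall may not be exact, and uses an SD of 5, a significance level of 0.05 and 80% power. The 17 per arm does not depend on the 3.6 mmol/L, and a fall of 2.6 or 3.6 lies inside the margin either way.
- **A real hourly reading of the table.** The caption, the column header and the Example (47 × 30 = 1410 ml over 24 h) all settle the unit as 24 h. The phrase about hourly periods is a wording slip.

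**Conclusion.** The point holds as an inconsistency in how the intervention is described. By the protocol's own formula, Table 1 delivers about 80% of maintenance from 10 to 24 kg, 83% at 30 kg and 86–87.5% from 50 kg, which is roughly 6% to 17% more fluid than three-fourths (79.6/75 = 1.06; 87.5/75 = 1.17). The regimen is not one common fraction of maintenance, as the abstract, the Background and the Parenteral Fluid Therapy section present it. The consequence is confined to the stated degree of restriction and the rate to which the results can be generalised. The conclusion rests on reading the formula in weight bands, which the 1700 cal behind the Example's insensible losses confirms, and on 1 ml per cal, which the protocol states. Nothing here says which of the three statements is the intended one.

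**What to change.** Before enrolment, reconcile Table 1, its attribution to the Holliday-Segar formula and the stated fraction; which of them changes is for the clinical team to decide. State in the protocol, and later in the report, the actual percentage of maintenance by body weight. Change the wording about hourly periods to per 24 h, as an editorial correction.

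If only the label or attribution changes, the Example stands, because it already uses the table volume. If the table volumes change, rerun the Example and update the predicted fall that the Sample size calculation section quotes.

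The cost is a few lines of text or a recalculated table and, in the second case, a short recalculation. The arms, the analysis and the number of patients stay the same. The protocol invites comments before the study starts, so the correction can be made at that stage.

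### The planned osmolality-based prediction of 24 h plasma sodium divides infused electrolytes only by total urine osmolality, so it tends to understate urine volume and overstate the fall

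*Protocol article*

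**What the plan says.** All of the relevant text is in the protocol article, under Parenteral Fluid Therapy, Example and Sample size calculation.

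- **Definition of the load.** Parenteral Fluid Therapy says that replacement of urinary water depends on "the renal solute load, i.e., the total daily excretion of solutes, and the concentration of these solutes in the urine". It then cites "a solute load of 40 mosmol/100 cal per 24 h, a figure expected in the instance of rational parenteral fluid therapy".
- **Load used for prediction.** Later in the same section, the infused sodium, potassium and chloride are supposed to "represent the renal solute load that eventually will be excreted in the urine". Glucose is set to zero. So is acetate, because "this anion is metabolized in the liver and does not contribute to renal solute load".
- **Worked example.** For a 30 kg child in the 0.23% arm, Example divides a "solute load of 169.2 mosmol" by a urine osmolality of 900 mosmol/kg. It obtains 188 ml of urine, 457 ml of retained water and a 24 h plasma sodium of 136.5 mmol/L.
- **Use in the trial.** The study will examine whether plasma sodium at 24 h "can be correctly estimated by using the patient's immediate postoperative urine osmolality value", "by applying the same approach as described in our hypothetical case". This estimate and one from the measured water and electrolyte balance will each be plotted against the measured 24 h value.
- **Use in the sample size section.** The largest fall that this algebra gives, 3.6 mmol/L in the 0.40% arm, is cited when the 5 mmol/L margin is introduced.

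**The concern.** Urine volume equals solute excreted divided by urine osmolality only when both terms count the same solutes. Measured osmolality counts all of them, including urea. The planned numerator counts only what was infused as sodium, potassium and chloride. This conflicts with the article's own definition of renal solute load. For the example child, the numerator is also about a quarter of the load that the article's own figure implies.

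If the numerator is too small, the computed urine volume is too small, the computed water retention is too large and the predicted sodium is too low. The analysis asks whether an early urine osmolality can predict sodium at 24 h. If the rule agrees poorly with the measured values, the result could not tell apart two explanations: that early osmolality is a poor predictor, or that the formula around it was mis-specified. The same algebra also supplies the 3.6 mmol/L fall quoted in Sample size calculation.

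**Working it through.** **Inputs from the protocol article (30 kg child)**

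- Energy expenditure: 1500 + 20 × 10 = 1700 cal, that is 17 units of 100 cal
- Infused volume: 1410 ml
- Insensible loss: 45 × 17 = 765 ml
- Water left for urine at zero balance: 1410 − 765 = 645 ml
- Total body water: 0.60 × 30 = 18 L
- Initial sodium: 140 mmol/L, so 18 × 140 = 2520 mmol
- Urine osmolality: 900 mosmol/kg

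**Formulas**

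- Urine (L) = solute load ÷ osmolality
- Retained water = 0.645 L − urine
- Predicted sodium = 2520 ÷ (18 + retained water)

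**Step 1. The plan's own figures**

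- 0.23% arm: 1.41 × (40 + 20 + 60) = 169.2 mosmol; ÷ 900 = 188 ml; retained 457 ml; 2520 ÷ 18.457 = 136.5.
- 0.40% arm: 1.41 × (70 + 45) = 162.15 mosmol; 180.2 ml; retained 464.8 ml; 136.48 (stated 136.4, a rounding difference).
- 0.81% arm: 1.41 × (140 + 4 + 118) = 369.4 mosmol; 410.5 ml; retained 234.5 ml; 138.2.

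The stated results reproduce, so the arithmetic is sound. The question is the choice of numerator.

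**Step 2. The article's own total load**

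40 × 17 = 680 mosmol. The example uses 169.2 ÷ 17 = 9.95, about 10 mosmol/100 cal. With 680 mosmol, urine is 680 ÷ 900 = 756 ml, water balance is 645 − 756 = −111 ml, and predicted sodium is 2520 ÷ 17.889 = 140.9. The predicted fall of 3.5 disappears.

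**Step 3. A range for non-infused solute**

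The article does not give non-infused solute separately, so 5 to 30 mosmol/100 cal is assumed. The top of the range is 40 minus the roughly 10 that is infused. Results are for the 0.23% arm at 900 mosmol/kg.

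| Added solute (per 100 cal) | Total load (mosmol) | Urine (ml) | Water balance (ml) | Predicted sodium (mmol/L) | Difference from 136.53 |
|---|---|---|---|---|---|
| 0 (plan) | 169.2 | 188 | +457 | 136.53 | 0 |
| 5 | 254.2 | 282 | +363 | 137.24 | 0.7 |
| 10 | 339.2 | 377 | +268 | 137.95 | 1.4 |
| 20 | 509.2 | 566 | +79 | 139.39 | 2.9 |
| 30 | 679.2 | 755 | −110 | 140.86 | 4.3 |

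**Step 4. Does the bias depend on osmolality?**

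Take 600 mosmol/kg and 10 mosmol/100 cal of added solute. The plan's rule gives 169.2 ÷ 600 = 282 ml and 137.23; the fuller load gives 339.2 ÷ 600 = 565 ml and 139.38. The difference is 2.2, against 1.4 at 900. The bias varies with the predictor itself, so it is not a constant offset.

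**Step 5. Can other errors reverse it?**

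Both checks use assumed inputs, with 10 mosmol/100 cal of added solute.

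- *Osmolality rises after surgery.* With 300 mosmol/kg at the start, the plan's rule gives 564 ml and 139.4. If osmolality is then 900, the balance gives 377 ml and 138.0. Here the rule overstates urine and predicts too small a fall.
- *Net cation loss of 60 mmol, with its anion, at 900 mosmol/kg.* The load is 339.2 + 120 = 459.2 mosmol, urine is 510 ml and water balance is +135 ml. Sodium is (2520 − 60) ÷ 18.135 = 135.7, against 136.5 by the rule. The rule again predicts too small a fall.

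**The case against.** **The article admits the limits and tests the rule.** It says that a fixed osmolality and counting inputs only may limit accuracy, adds a measured-balance estimate, and asks whether the simple rule works. A biased rule could be seen on the agreement plot, and rejecting it would be correct. This lowers the stakes but does not remove the defect. The caveat names neither the missing solutes nor the direction of error, and the rule is then carried forward unchanged. A plot showing disagreement would not say whether the early osmolality or the numerator was at fault.

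**The load of 40 mosmol/100 cal is a cited figure for rational parenteral therapy, not a measurement in these children.** This stands, and it is why the size is given as a range with 4.3 mmol/L at the top.

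**Four stronger readings are tempting but not supported.**

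- *The rule predicts too large a fall in every child.* Step 5 shows that rising osmolality or net cation loss can offset or reverse the error.
- *A bias of 4.3 is nearly the whole 5 mmol/L margin.* The margin is a difference between treatment groups in observed sodium. The bias is an error in predicting one child's value. The two are not comparable.
- *The sample size rests on a faulty fall.* Sample size calculation calls the margin arbitrary, warns that the 3.6 may not be exact, and derives 17 per arm from a difference of 5 and an SD of 5.
- *The balance equation omits insensible loss, because the change in body water "describes the water infused minus water excreted, respectively".* The equations are not shown in the available text, the article says that insensible loss will be calculated for each participant, and excreted water need not mean urine alone.

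**Conclusion.** The point holds as a defect in a secondary analysis. The planned rule sets an electrolyte-only numerator over an all-solute denominator and contradicts the article's own definition of renal solute load. If its other assumptions are met (osmolality constant from the end of surgery, no net sodium change), it tends to understate urine volume and overstate the fall in sodium.

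For the 30 kg child in the 0.23% arm at 900 mosmol/kg, the bias is about 0.7 to 4.3 mmol/L, set against a predicted fall of only 3.5. The range rests on the assumed 5 to 30 mosmol/100 cal of non-infused solute; the top corresponds to the article's own total of 40. The primary ANCOVA does not use the prediction, and the margin and the sample size stand.

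**What to change.** 1. Add a second prediction that compares like with like, and keep the plan's rule as comparator. There are two options:
   - put a total solute load in the numerator, for example the article's 40 mosmol/100 cal, with a sensitivity range; or
   - divide infused sodium plus potassium by the urinary sodium plus potassium concentration in the first post-operative spot sample. This works only where that concentration is measurable, since the article itself notes that urinary sodium can be undetectable when extracellular volume is contracted.
2. Rerun the worked example for the three arms with the fuller load beside the present one.
3. In Sample size calculation, describe the 3.6 mmol/L fall as an upper-end estimate under an electrolyte-only load. The margin and the number per arm stay as they are.

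The cost is recalculation plus either one further stated assumption (the solute load) or at most one added spot urine potassium result. Sodium in that sample is already needed for the fractional excretion of sodium. Enrolment had not begun when the article was written and it invites comments, so the change can be made in time.
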